
Outside the context of MBPs, regular mindfulness meditation dose-response investigations have focused primarily on the relationship between cumulative practice time over the course of an intervention and outcomes. In experimental conditions, such variation in practice time has arisen from natural differences across participants rather than systematic manipulations. While most [13-15], though not all [16], studies support a positive association between time spent practicing and outcomes, such findings may be subject to bias due to the nonrandom distribution of participants across different practice doses. In low-dose settings, while benefits have been demonstrated from single short sessions approximating 15 minutes [17], the measures used in such studies have tended to focus on transient or *state* effects that are more sensitive to change. Therefore, it is not clear what minimum dose is required for efficacious practice when measures focus on trait effects related to the psychological domains that most often motivate practice [18]. In addition, while it is likely that participants in high-dose settings such as meditation retreats represent individuals who derived enduring benefits from the practice, as evidenced by exceptional traits in several psychological and cognitive domains [19], such results may be biased by self-selection [20]. Therefore, there is a lack of empirical work in which practice doses are systematically varied in such a way as to enable differential effects to be causally linked to different practice doses. Moreover, because of this, there is a concomitant lack of empirical evidence of the merits of different practice doses given an individual’s circumstances and disposition and knowledge of the trade-offs from recommending higher and lower doses.

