#### Weekly Measures

During the intervention period, additional measures will be obtained weekly (ie, 7, 14, 21, and 28 days after the baseline survey).

*Mindfulness* practice will be assessed using the following items: (1) “In the past week, how many daily sessions of this study’s meditation program did you complete?” (response options: 0-7); (2) “In the past week, on the days you meditated with the study program, approximately how many minutes (on average) was each meditation session?”; (3) “In the past week, how many additional days did you practice meditation?” (response options: 0-7) and “In the past week, on the days you meditated in addition to the study program, approximately how many minutes (on average) was each meditation session?”; (4) “On the days you practised meditation, how many minutes per session did you practice? (this includes the guided sessions in the meditation program)” (response options: 0 to ≥60 min); and (5) “In the past week, how often did you engage in informal mindfulness practice? i.e. mindfully washing dishes, showering, walking etc.” (response options: none of the time to all of the time).

*Adverse events* will be assessed using a modified short form of the Meditation-Related Adverse Effects Scale [50].

*Sleep* will be assessed using a single item from the Sleep Quality Scale [33]: “During the past week, how would you rate your sleep quality overall?” (response options: *terrible*=1, *poor*=2-4, *fair*=5-7, good=7-9, and *excellent*=10).

*Expectancy* will be assessed using the following item: “How effective do you think your training so far has been for your [goal or motivation free-text field from run-in survey]?” (response options: not at all effective to very effective).

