#### Efficacy Analyses

Analyses of all outcomes will also be conducted on a per-protocol basis to test the efficacy of different doses under “ideal” conditions of high compliance. The model will incorporate study visit (T0, T0.5, and T1; additional analyses will include T2) and intervention (10, 20, and 30 min each vs the minimal dose) as categorical variables. The per-protocol analysis sample will consist only of those participants who were compliant with the allocated intervention dose, excluding those who did not comply as opposed to reallocating them to an arm representing their actual dose. A “complier” will be defined by having reported session completion for >66.67% and <117% of sessions (100%=6 weekly sessions=24 sessions).

Estimation of effects in randomized controlled trials is known to be biased when there are variable rates of nonadherence to treatment [58]. To control for prerandomization factors that may influence nonadherence to the 10-, 20-, and 30-minute conditions, we will adjust for prerandomization confounders for the per-protocol analysis, such as personality traits (conscientiousness [59,60]), openness to experience [59,61], depressive symptoms [59,61], and motivations and expectations [60]. The method of inverse probability weighting will be used to control for confounding bias due to prerandomization factors [62]. A causal diagram will be drawn to determine a priori potential pre- and postrandomization confounders associated with being a complier [58].

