#### Additional Analyses

If any difference between any conditions is observed for any of the primary or secondary analyses, we will explore ways of quantifying that relationship as a means of representing dose-response effects. In particular, we will test for the presence of a linear and log-linear relationship across the treatment doses.

We will describe differential rates of attrition and adherence across the different treatment arms and explore whether any variables collected at baseline predict differential attrition and adherence.

Using estimated practice time per adherence measures, we will implement a receiver operating characteristic analysis to ascertain the practice amount at which individuals achieve a change of ≥7.45 points on the primary outcome of the WEMWBS (estimated temporal SE of measurement of 2.69 [35] using a multiplier of 2.77 [63]) to detect a statistically important change at the individual level.

Further exploratory analyses will be conducted using both the intention-to-treat and per-protocol approaches on outcomes collected at weekly and biweekly intervals.

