### Strengths and Limitations

When compared to previous empirical dose-response assessments, our study has several notable strengths and some limitations. These are described in the following paragraphs.

Our study has several characteristics that will improve our capacity to make inferences about dose-response effects for mindfulness practices compared to previous studies that have tested dose-response effects for mindfulness meditation. Our targeted sample size (N≥866) is powered to detect small effects (*d*=0.2 approximately) between active dose conditions. The program length is 28 days, which will allow us to test for changes in more stable “trait” effects. There is considerable variation in doses for daily sessions, ranging from 10 to 30 minutes. These doses are based on a nonsystematic search of the literature, MBPs, and mindfulness apps with dosage recommendations (for details, refer to the study by Bowles et al [11]). The random allocation of participants to different doses will allow us to make inferences about the effects of different doses, which are less subject to bias than those in previous assessments [3,10]. Finally, while our primary outcome is well-being, we have a range of outcome measures covering different aspects of well-being and mental health, as well as hypothesized mechanisms of change for mindfulness interventions, including decentering and emotional reactivity.

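### The additional ROC analysis claims to find the practice amount that produces change, but its predictor is partly self-selected and it returns a cut-off even when dose has no effect

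*Protocol article*

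**What the plan says.** The plan for this analysis is one sentence under Additional Analyses. The predictor is fixed as practice actually done: "Using estimated practice time per adherence measures, we will implement a receiver operating characteristic analysis". The event is "a change of ≥7.45 points on the primary outcome of the WEMWBS", and the purpose is "to ascertain the practice amount at which individuals achieve a change".

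Practice is self-reported. The Weekly Measures section asks how many sessions were completed and "approximately how many minutes (on average) was each meditation session", and has separate items on practice outside the program.

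Three other places bear on this:

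- Background and Rationale says of earlier work on cumulative practice time that "such findings may be subject to bias due to the nonrandom distribution of participants across different practice doses".
- Strengths and Limitations presents randomization as the answer: "The random allocation of participants to different doses will allow us to make inferences about the effects of different doses".
- Efficacy Analyses names conscientiousness, openness, depressive symptoms, and motivations and expectations as influences on adherence, and says "we will adjust for prerandomization confounders for the per-protocol analysis". No such adjustment is stated for the ROC.

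The same Additional Analyses section makes its linear and log-linear dose tests conditional on an observed difference between conditions. The ROC paragraph carries no such condition.

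**The concern.** Session length is randomized, but the number of sessions completed is chosen by the participant. If motivated or conscientious people both practise more and improve more, achieved minutes will separate responders from non-responders even when practice does nothing. That is the bias the Background warns about, and it re-enters here through the adherence component of the predictor.

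A second problem is independent of confounding. A search for the best cut-off on an ROC curve yields a number whether or not the predictor carries information. Nothing in the ROC paragraph ties the reading of that number to a difference between randomized arms.

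The Discussion says the findings may help beginners and their advisors estimate the practice required for particular outcomes. A figure in minutes, described as the amount at which people achieve change, would readily be read as a required dose.

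**Working it through.** **The protocol's own figures.** The threshold reproduces: 2.69 × 2.77 = 7.451, stated as 7.45. From the Sample Size section, the SD of change is 9.84 × √(2 × (1 − 0.83)) = 5.74. With that SD, a 1.97-point difference, two-sided 0.02 and 80% power, the change-score formula gives 171 per arm against the stated 172. The inputs taken forward are therefore 4 × 172 = 688 participants and a change SD of 5.74.

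**What the predictor mixes.** With 24 guided sessions, the most program minutes available in each arm are 24 × 4 = 96, 24 × 10 = 240, 24 × 20 = 480 and 24 × 30 = 720. A cut-off of 210 minutes cannot be reached from guided sessions in the 4-minute arm. It needs 21 of 24 sessions at 10 minutes, 11 at 20 minutes, or 7 at 30 minutes. One number in minutes thus combines allocated arm with diligence.

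**Simulation with no effect of practice.** The following are assumptions, because the documents do not give them:

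- Mean change is 2 points in every arm, so the responder proportion is 1 − Φ((7.45 − 2)/5.74) = 1 − Φ(0.949), about 17%.
- Sessions completed = round(24 × Φ(0.9 × latent + 0.6)), and minutes = sessions × assigned length.
- One trait is correlated with the adherence latent and with change. Given the trait, change is independent of minutes.
- The cut-off maximizes sensitivity plus specificity.

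With P responders and Q non-responders, AUC = (rank sum of responders − P(P + 1)/2)/(PQ). Its null standard error is √((N + 1)/(12PQ)). Here P is about 118 and Q about 570, so the standard error is √(689/807,120) = 0.029. An AUC beyond about 0.5 + 1.96 × 0.029 = 0.557 is then nominally significant.

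Results at 1,500 trials per scenario (ranges are across repeat runs):

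| Trait–adherence, trait–change correlation | Mean AUC | Nominally significant |
|---|---|---|
| 0, 0 | 0.500 | about 5–6% |
| 0.3, 0.2 | 0.516 | about 8–9% |
| 0.5, 0.3 | 0.538 | about 25–27% |
| 0.6, 0.4 | 0.56 | about 53–55% |
| 0.6, 0.5 | 0.573 | about 70% |

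With no confounding the median cut-off was about 200 minutes, with an interquartile range of 84 to about 405. That range runs from a value attainable in the 4-minute arm (21 × 4 = 84) to one beyond the 10-minute arm's maximum of 240. In the confounded scenarios the median was about 210.

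**A second adherence model.** Here adherence falls with dose, as the Discussion expects, and the trait drives adherence directly. There is again no effect of practice. Without confounding, a cut-off was returned in every one of 1,000 trials per setting, with a median of 210–230 minutes and a 5th–95th percentile range of about 50 to 600. With trait–change correlations of 0.2, 0.3 and 0.5, mean AUC was about 0.53, 0.55 and 0.58. It was nominally significant in 18–25%, 30–47% and 61–87% of trials, and the median cut-off rose to about 320, 340–360 and 380 minutes. These ranges cover mean changes of 0, 2 and 4 points. Within the 20-minute arm alone, where all variation in practice is self-selected, AUC was 0.58–0.60, 0.62–0.64 and 0.70–0.73.

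**The case against.** Five counter-arguments deserve weight.

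- **Role.** A reader might infer that the ROC is the trial's main answer to how much practice is needed. The documents do not support that. General Principles places the main purpose in the intention-to-treat comparison of prescribed doses. The ROC is an additional analysis on which no primary or secondary conclusion depends. This stands.
- **Same flaw as earlier studies.** A reader might also infer that the ROC simply repeats the design the Background criticises. It does not. In the first adherence model above, randomized arm explains about 67% of the variance in minutes, so the contamination is partial. This stands, though dilution does not remove the bias.
- **Strength of confounding.** The correlations are assumed, and mild ones give only 8–9% significance. In the first model mean AUC never passes 0.573, no simulated trial in the strongest scenario reached 0.70, and the median cut-off hardly moves (200 against 210). Those results therefore do not show that confounding creates the threshold. In the second model the median does move, so this depends on the adherence model.
- **Cut-off always returned.** This is true of any ROC, and with no confounding the AUC correctly sits at 0.50. The protocol names no cut-off rule. The rule and its interval may properly sit in an analysis plan that is not shown, so their absence is not the criticism. The criticism is the stated aim combined with the stated predictor.
- **Existing analyses.** Mean differences with 95% CIs between arms and dose trends are already planned. They do not report the proportion reaching 7.45 points by arm.

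**Conclusion.** The point holds as a limited one about an additional analysis. The ROC as described can show that achieved minutes and individual improvement go together. It cannot establish the amount at which individuals achieve the change, because the predictor is part randomized and part self-selected, no adjustment is stated, and nothing makes its reading conditional on a randomized difference.

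Two sizes should be kept apart. That a cut-off emerges under no effect, over a range as wide as 84 to 405 minutes, does not depend on any confounding assumption, although the exact range depends on the adherence model and cut-off rule. The false signal in the AUC does depend on assumed confounding: AUC 0.52 to 0.57 with about 8% to 70% nominal significance in the first model, and up to 0.58 and 87% in the second. The protocol's figures cannot place the trial within that span.

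The primary intention-to-treat result and the sample size are unaffected.

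**What to change.** - **Main individual-change result.** Report the proportion reaching 7.45 points or more by randomized arm, with a baseline-adjusted trend across assigned dose and a 95% CI.
- **ROC.** Keep it as a descriptive association. Adjust or weight it for the baseline confounders listed under Efficacy Analyses, give the AUC and a bootstrap interval for the cut-off, and interpret the cut-off as a threshold only if the randomized arms differ.
- **Wording.** Replace the stated aim with one that describes an association between achieved practice time and individual change, and acknowledge self-selection.
- **Instrumental-variable estimate.** Using randomized arm as an instrument for minutes is at most optional. The active arms also differ in practice points (5, 10 and 15 per session) and in the share of spoken content (62%, 47% and 40%), so arm may affect outcome other than through minutes.

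The cost is a little extra analysis on variables already scheduled for collection, and a less definite practice threshold. One practical matter is that the run-in can be passed on 4 of 7 days, while personality is collected on days 2 and 3 and motivation on day 4. Some confounder values may therefore be missing and will need handling.

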#### Multiple Testing Adjustment

For the analysis of the primary outcome, we will use a Bonferroni adjustment to control the type I error rate for the primary outcome across all 3 pairwise comparisons by setting the 2-sided significance level at .02. For analyses of secondary outcomes, with nominal α set at *P*<.05, we will adjust for multiple comparisons at the variable level using the false discovery rate procedure [64], which is less conservative than the Bonferroni correction and, therefore, may provide a better balance than Bonferroni between the likelihood of type 1 and type 2 errors.

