### Sample Size

A meta-analysis of meditation apps [1] indicates a standardized mean difference (SMD) effect size of 0.29 (95% CI 0.14-0.45) for psychological well-being when comparing apps to controls. A more recent study [6] randomized participants to approximately 10 or 30 minutes of sitting or movement practice for 2 weeks. They estimated a difference in the effects on the WEMWBS between the sitting groups of short and long duration of SMD=0.2 to 0.25. To be conservative, we determined a target sample size with an SMD of 0.2.

On the basis of an SD in WEMWBS scores of 9.84 [55] and a within-individual correlation of 0.83 in repeated assessments of the WEMWBS [34], we would need a final sample size of 688 participants to achieve 80% power (at the 2-sided *P*=.02 significance level to correct for multiple comparisons between conditions) to detect a difference of 1.97 points (SMD=0.2) for each active condition (10, 20, and 30 min) compared to one another and with the minimal-dose condition. This would translate to approximately 172 participants per arm. These calculations were conducted using the *sampsi* package in Stata (StataCorp).

Meditation app studies indicate overall retention rates of approximately 60% for active mindfulness meditation interventions [1]. Given our use of a run-in period, the aim of which is to allow participants who are most likely to disengage to do so before randomization, we anticipate postrandomization retention rates approximating 80%. In total, we will then recruit on a rolling basis until we achieve the required sample size at randomization of 860.

We will aim to recruit the full sample by March 31, 2025. We will conduct an interim analysis at this stage if the sample is at <90% of the target. If the sample is at ≥90% of the target by March 31, 2025, recruitment will be terminated. If continued recruitment is necessary (ie, we recruit <90% of the sample by March 31, 2025), recruitment will continue until the target sample is reached or 6 months (from March 31, 2025) have elapsed (whichever occurs first). If an interim analysis is required, the team member who undertakes this analysis will not implement the final analysis (as they will need to be unblinded). Other members of the team will undertake the final analysis and will alter the arm designation in the analytic code to further blind results relative to the interim analysis.

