### Statistical Methods

#### General Principles

The primary analysis will be undertaken on the primary outcome following the intention-to-treat approach [56]. The intention-to-treat analysis sample will consist of all randomized participants, assigning them to the arms they were randomized to independently of their subsequent behavior. An intention-to-treat approach was chosen for the primary analysis because the study’s main purpose is to test whether larger *prescribed* doses of mindfulness practice yield larger effects on well-being. Intention-to-treat analyses will also be conducted for all secondary outcomes. Additional secondary analyses will be conducted following the per-protocol approach for all outcome measures (ie, primary and secondary). For data collected at weekly increments between T0 and T1, measurement occasions will be nested within individual participants.

The comparisons of interest will be each intervention (10, 20, and 30 min) compared to one another and with the minimal dose for each outcome (mean difference and 95% CI).

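### The primary contrasts are tested by single-step Bonferroni, although Holm's step-down test on the same contrasts controls the same family-wise error and never rejects fewer

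*Protocol article*

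**What the plan says.** The Multiple Testing Adjustment section states: "we will use a Bonferroni adjustment to control the type I error rate for the primary outcome". It counts three pairwise comparisons, and it makes the adjustment "by setting the 2-sided significance level at .02". Every contrast therefore faces the same threshold whatever happens to the others. No step-down, closed or gatekeeping procedure is named for the primary outcome, and no reason is given for the single-step form. For secondary outcomes the same section chooses a false discovery rate procedure because it is less conservative than Bonferroni.

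The Sample Size section uses the same level ("at the 2-sided *P*=.02 significance level to correct for multiple comparisons between conditions") and concludes: "we would need a final sample size of 688 participants to achieve 80% power". The General Principles section describes the active doses as "compared to one another and with the minimal dose for each outcome (mean difference and 95% CI". It mentions no adjustment of the intervals.

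**The concern.** Bonferroni holds every contrast to the strictest threshold even after another has been rejected. Holm's first step is the Bonferroni test, and each later step only relaxes the threshold. At a common family-wise bound, Holm therefore cannot reject fewer hypotheses and sometimes rejects more.

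The usual reason to stay with the single-step form is that it has matching simultaneous intervals. The protocol plans 95% intervals without adjustment, so it makes no use of that advantage.

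What is at stake is power that costs no participants. The article reports 70 eligible participants enrolled by the end of 2024, against 860 to be randomized.

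**Working it through.** **Inputs (Sample Size section).** SD 9.84; within-person correlation r = 0.83; difference 1.97; 172 per arm; two-sided level .02; power 80%; retention 80%.

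**The plan's own figure.** The variance of a change score is SD² × 2(1 − r) = 96.83 × 0.34 = 32.92. Then n per arm = 2 × 32.92 × (2.326 + 0.842)² / 1.97² = 170.3, so 171 against the stated 172. Power at 172 per arm is 80.4%. Also 688 / 0.8 = 860. The stated figures reproduce.

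**A second variance.** The primary model constrains the baseline means to be equal, so its efficiency is closer to ANCOVA: SD² × (1 − r²) = 96.83 × 0.3111 = 30.12. Power at .02 is then 84.2%. Both variances are carried below.

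**Procedures compared.** Bonferroni tests all three P values at .05/3 = .0167. Holm takes the ordered P values against .05/3, .05/2 and .05, stopping at the first failure. Power was obtained by simulating four arm means with variance 32.92/172 or 30.12/172 (600,000 draws) and applying z tests.

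**Three active-versus-minimal contrasts, all three doses 1.97 above minimal:**

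| Variance | Quantity | Planned .02 | Bonferroni, .05 | Holm, .05 |
|---|---|---|---|---|
| Change score | Power per contrast | 80.4% | 78.5% | 85.2% |
| Change score | All three found | 62% | 59% | 75% |
| ANCOVA | Power per contrast | 84.2% | 82.5% | 88.5% |
| ANCOVA | All three found | 68% | 65% | 80% |

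At the same bound the gain is 6 to 7 points per contrast. The planned .02 is .05/3 rounded up, with a nominal bound of 3 × .02 = .06, so the net gain from the plan to Holm at strict .05 is smaller: 85.2 − 80.4 = 4.8 and 88.5 − 84.2 = 4.3 points.

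**In participants.** For Bonferroni at .0167 to reach 85.2% under the change-score variance, n = 2 × 32.92 × (2.394 + 1.045)² / 1.97² ≈ 201 per arm. That is 29 more per arm, 116 in total, or 116 / 0.8 = 145 more randomized.

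**Other true patterns (three contrasts, family-wise .05, Bonferroni to Holm):**

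| True pattern | Contrast with minimal | Change score | ANCOVA |
|---|---|---|---|
| Linear: 0, 0.66, 1.31, 1.97 | 10 min | 9.3% to 16.3% | 10.0% to 17.6% |
| | 20 min | 39.4% to 45.4% | 43.1% to 49.3% |
| | 30 min | 78.6% to 79.5% | 82.5% to 83.4% |
| Only 30 min effective | 30 min | 78.6% to 78.7% | 82.5% to 82.6% |

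In these two patterns Holm at strict .05 leaves the 30-minute contrast slightly below its power at the planned .02 (80.4% and 84.2%), because .02 is the looser level.

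**False positives.** With no true differences, Bonferroni and Holm have the same family-wise error, 4.5%. If 10 min equals the minimal dose and the other two doses are 1.97 better, the chance of falsely declaring 10 min effective is 1.7% with Bonferroni and about 4% with Holm. With those two effects doubled to 3.94, Holm reaches .050, its bound.

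**If the family is all six pairs.** After one rejection among four means, at most three pairwise nulls can still be true together. Shaffer's thresholds are therefore .05/6, then .05/3 three times, then .05/2, then .05. With all three doses 1.97 above minimal, power per active-versus-minimal contrast is:

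| Variance | Bonferroni | Holm | Shaffer |
|---|---|---|---|
| Change score | 70.8% | 73.7% | 76.9% |
| ANCOVA | 75.5% | 78.3% | 81.2% |

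All are below the power at .02, but six tests at .02 have a family-wise error of about 9.2% when no dose differs.

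**The case against.** The strongest reply is that this is a preference. Bonferroni is a valid procedure, it is prespecified, and the trial is sized at the level it uses, so the plan has already paid for its adjustment. That stands, and it limits the point to lost efficiency.

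A reader might also infer that the trial gives up about 6 points on every contrast for nothing. The documents do not support that:

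- The 6 points belong to a plateau in which all three doses are equally effective. Hypothesis 1 expects larger doses to do more, and then the gain falls mainly on the weaker contrasts, which stay below 50% power.
- The extra rejections have a price. When some doses work and others do not, an ineffective dose is more often declared effective, which matters in a trial asking how much practice is needed. The rate stays within the family-wise bound.
- Step-down tests have no simple matching simultaneous intervals.

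Nor does slow recruitment by itself show a power shortfall, since the Sample Size section allows up to six further months.

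Finally, the family is not settled. The adjustment section counts three comparisons, while the Sample Size and General Principles sections name the doses against one another as well, which makes six. That is a separate question, but it decides which step-down rule applies and must be answered first.

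**Conclusion.** The point holds as an inexpensive improvement that should be made. At a common family-wise bound Holm dominates single-step Bonferroni. At the plan's sizing assumptions, with all three doses 1.97 points above minimal, it adds 6 to 7 points of power per contrast and about 15 points to the chance of finding all three. Against the planned .02 the net gain per contrast is 4 to 5 points.

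These sizes rest on 172 analysable participants per arm, SD 9.84, r = 0.83, the three contrasts with the minimal dose, and equal true effects. The gain is uneven under a gradient and close to nil if one dose alone works. With all six pairs at strict .05, even Shaffer's rule gives less power than the planned .02. Nothing here shows that the planned Bonferroni method fails to control type I error.

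**What to change.** Settle the family first, then change one sentence in Multiple Testing Adjustment.

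- **Three active-versus-minimal contrasts:** replace the Bonferroni adjustment at .02 with Holm's procedure at family-wise two-sided .05, comparing the ordered P values with .05/3, .05/2 and .05. Report adjusted P values.
- **All six pairs:** use Shaffer's step-down (.05/6, .05/3 three times, .05/2, .05), report adjusted P values, and restate the power in Sample Size. It is about 77-81% per active-versus-minimal contrast when all three doses are 1.97 above minimal.

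The change needs no additional participants. Its costs are that the reported intervals will not match the step-down tests, which the protocol should say, and a higher per-contrast false positive rate when only some doses work, still within family-wise .05.

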#### Effectiveness Analyses

A constrained longitudinal data analysis method [57] will be used to build the linear mixed-effects model estimating the effect of the interventions on the primary outcome. The model will incorporate study visit (T0 and T1) as a categorical variable, intervention (10, 20, and 30 min each vs the minimal dose), and intervention by study visit interaction as main effects. The model will assume a common baseline mean of the outcome across the 4 intervention groups and an unstructured variance-covariance among the repeated measurements.

Models analyzing secondary outcomes will incorporate study visit (T0, T0.5, and T1) and intervention (10, 20, and 30 min each vs the minimal dose) as categorical variables. Secondary continuous outcomes will be analyzed similarly to the primary outcome (ie, the constrained longitudinal data analysis described previously). Additional analyses will include follow-up assessments (ie, T2) in the model.

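### The primary-outcome significance level of .02 is set for 3 comparisons, but the plan names 6, so the family-wise error is about 9%, not 5%

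*Protocol article*

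**What the plan says.** Four places in the protocol article bear on which primary tests are made and at what level.

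- **Multiple Testing Adjustment** fixes the method, the count and the level. Bonferroni is used, as that section puts it, "to control the type I error rate for the primary outcome across all 3 pairwise comparisons by setting the 2-sided significance level at .02".
- **Statistical Methods, General Principles** defines what is compared: "The comparisons of interest will be each intervention (10, 20, and 30 min) compared to one another and with the minimal dose for each outcome".
- **Sample Size** powers the trial at the same two-sided .02, described as a "significance level to correct for multiple comparisons between conditions", and claims 80% power to detect 1.97 points "for each active condition (10, 20, and 30 min) compared to one another and with the minimal-dose condition".
- **Effectiveness Analyses** writes the primary model with "intervention (10, 20, and 30 min each vs the minimal dose), and intervention by study visit interaction as main effects".

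The article describes no gatekeeping, fixed testing order or global test that would protect comparisons outside the 3 that are counted.

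**The concern.** A Bonferroni level depends on the number of tests. Two sections describe all pairs among four arms, while the section that sets the level counts half of them. If all the named pairs are tested at .02, the claim that type I error on the primary outcome is controlled is not met.

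The active-versus-active pairs cannot be treated as incidental:

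- The first hypothesis is that larger doses have larger effects.
- The planning effect size was set with reference to a study comparing about 10 with about 30 minutes.
- Strengths and Limitations presents power between active doses as an advantage of the trial.
- Under Additional Analyses, a difference between any conditions leads on to linear and log-linear dose-response tests, so a false positive on any pair carries forward.

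The power claim depends on the same level. If the level is wrong for the family, so is the 80%.

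**Working it through.** **Inputs (protocol article).** Four arms with equal allocation; two-sided level .02; SD 9.84; within-person correlation 0.83; difference 1.97; 172 per arm (688 in total). The 5% family-wise target is an inference from the use of Bonferroni, because .05 is written only as the nominal level for secondary outcomes.

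**1. The plan's own sample size.** Change-score variance: 9.84² × 2(1 − 0.83) = 96.83 × 0.34 = 32.92, so the SD is 5.738.

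n per arm = 2 × (2.326 + 0.842)² × 32.92 / 1.97² = 170.3, rounded up to 171. The plan states 172, so its figure is reproduced to within one participant per arm, at level .02.

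**2. Number of comparisons.** Active versus minimal dose: 10–4, 20–4, 30–4. Active versus active: 10–20, 10–30, 20–30. Total 4 × 3 / 2 = 6.

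**3. Bonferroni levels.** For 3 tests, .05/3 = .0167. For 6 tests, .05/6 = .0083. The level .02 is neither of these; it is .0167 rounded up to two decimals. The Bonferroni bounds at .02 are 3 × .02 = 6% and 6 × .02 = 12%.

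**4. Family-wise error when all four arms are equal.** The pairs share arms, so the tests are correlated and the true figure lies below the bound. For all 6 pairs it is the upper tail of the studentized range with k = 4 at 2.326 × √2 = 3.290. For 3 comparisons with a shared control (correlation 0.5) it was found from 4 million simulated draws, which also confirmed the 6-pair result.

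| Level | 6 pairs | 3 versus minimal dose |
|---|---|---|
| .02 | 9.2% | 5.3% |
| .0167 | 7.8% | 4.4% |
| .0083 | 4.1% | 2.3% |

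Correcting only the rounding takes the 6-pair figure from 9.2% to 7.8%. The remaining excess comes from counting 3 instead of 6.

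**5. Power per pair at 172 per arm.** Power = Φ(1.97/SE − z), with SE = SD × √(2/172).

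- Change score: SE = 5.738 × 0.1078 = 0.619; 1.97/0.619 = 3.184.
- Baseline-adjusted: SD = 9.84 × √(1 − 0.83²) = 5.488; SE = 0.592; 1.97/0.592 = 3.329.

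| Level | z | Change score | Baseline-adjusted |
|---|---|---|---|
| .02 | 2.326 | 80.4% | 84.2% |
| .0167 | 2.394 | 78.5% | 82.5% |
| .0083 | 2.638 | 70.7% | 75.5% |

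**6. Holm instead of single-step Bonferroni.** The .0083 row is the first step of Holm and so a floor for it. In simulation at 172 per arm, with one arm differing from the other three by 1.97, Holm over 6 pairs gives about 74% (change score) or 78% (baseline-adjusted) for each true difference.

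**The case against.** The best explanation of the 3 is the primary model, which is coded as each dose against the minimal dose. If only those contrasts are confirmatory, the family-wise error at .02 is 5.3%, and the 9% does not apply. This explains how the count may have arisen, but it does not remove the conflict. Coding against a reference arm does not define a testing family. General Principles does define the comparisons of interest, and Sample Size agrees with it. If 3 was meant, those two sections are wrong and the active-dose pairs have no stated error control.

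Three further points stand as limits on the size of the finding:

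- The 9.2% is the worst case, with all arms equal. If one arm differs from three equal ones, the chance of a false rejection among the 6 pairs at .02 is about 5.2%. Equality of all arms is nevertheless the usual benchmark for a claim of family-wise control.
- The rounding from .0167 to .02 is minor on its own.
- The sample size is arithmetically sound at .02. If only 3 comparisons are meant, correcting the level costs about 2 points of power.

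**Conclusion.** The concern holds. The section that sets the level counts 3 primary comparisons, while the sections that define and power the comparisons describe 6, and .02 is not a 5% Bonferroni level for either number. For the comparisons as named, the family-wise error is 9.2% under equality of all arms, nearly twice the implied 5%. If the family were only the 3 comparisons with minimal dose, it would be 5.3%. These figures assume equal arm sizes, a normal approximation and an intended family-wise level of 5%.

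This should be settled before unblinding. Otherwise, any primary result with P between .0083 and .02 will be open to dispute. The plan itself fixes the count, the method and the level, and they conflict, so this is not a detail deferred to a statistical analysis plan.

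**What to change.** Choose one family and make General Principles, Effectiveness Analyses, Multiple Testing Adjustment and Sample Size agree with it.

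- **Option A, all 6 pairs confirmatory.** Replace the fixed .02 with Holm across the 6 pairs at a family-wise .05 (first step .0083). Restate power as at least 71% (change score) or 76% (baseline-adjusted) per pair, labelled as the first-step floor. This fits the dose-response aim best.
- **Option B, 3 comparisons with minimal dose confirmatory.** Test them at .0167, or by Dunnett or Holm, and call the active-versus-active pairs secondary. Restate power as 79% (change score) or 83% (baseline-adjusted) at .0167. The statement in Strengths and Limitations about power between active doses would then need to be toned down, since those pairs would no longer be confirmatory.

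State the 5% family-wise target for the primary outcome explicitly in either case.

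The cost is wording and a less favourable power figure. The correction does not require more participants. For information, holding 80% at .0083 would take 206 per arm (824 final, 824/0.8 = 1,030 randomised) by the change-score formula, or 188 per arm (752 final, 752/0.8 = 940 randomised) with baseline adjustment, against the planned 860. Accepting the lower power and stating it is the simpler course.
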